### 8. Data management

#### a) Methods (e.g. CRF) for data entry and collection

All data will be entered in excel and physical copies will be scanned as a pdf file. During the investigation, data will be saved on the VUB share point, which has a built-in back-up. After the investigation, data will be anonymized where possible and stored in the VUB university archive.

Option to access the database will require a data use agreement. The stored data will remain unchanged and be identified by the researcher ORCID and article DOI. Transfer of data will only be done if essential.

#### b) Procedures used for CRF tracking

The pre-processing (basic filters and artefact removal) steps will be performed by the co-investigators to ensure data quality.

#### c) Procedures for verification, validation and securing of electronic clinical data systems

The non-invasive brain MRI-scan will be taken under the supervision of [name]. [name], who is the department head of Radiology.

#### d) Procedures to maintain and protect subject privacy

As personal information is branded by the EU as sensitive, data will be anonymized as soon as possible. Participants will receive a code corresponding to their inclusion order, and the file that relates these codes to their personal information will be encrypted. During the course of the study, data will only be stored with personal access, on a personal cloud server. After the study completion, all data will be shared with the research lab through a network attached storage.

As personal and sensitive data of human participants will be collected, pseudonymisation of the data will take place as soon as possible upon data acquisition. The file which establishes the link between the pseudonymised identities and the identification of the participant, will be password-protected.

The data protection officer of the VUB ([contact]) will be notified of our study. Data in the present study will be managed confidentially, conforming to the Algemene Verordening Gegevensbescherming (GDPR) of 27 April 2016.

Participating in this study means that the participant agrees that the investigators gather data of the participant that will be used to conduct the investigation and eventually will result in the publications in scientific journals and presentations at conferences. The participant will always have the right to ask the investigators which data he/she has gathered on them and for what this data is used in light of the investigation. The participant retains the right to look into this data and to ask for corrections on the occasion this data would contain errors. The participant also retains the right to stop his/her participation in the study at any moment.

#### e) Methods for database locking at the start of the analysis and storage upon completion of the clinical investigation

All data will be entered in excel and physical copies will be scanned as a pdf file. During the investigation, data will be saved on the VUB share point, which has a built-in back-up. After the investigation, data will be anonymized where possible and stored in the VUB university archive.

Option to access the database will require a data use agreement. The stored data will remain unchanged and be identified by the researcher ORCID and article DOI. Transfer of data will only be done if essential.

### f) Procedures for data retention

All raw data will be stored in the online system of the Ethical Committee of the UZ Brussel (i.e., Redcap). Raw and cleaned data will also be stored and encrypted on the research's group network attached storage (NAS) under supervision of [name] [name]. The NAS is system-encrypted, back-upped, has up-to-date antivirus and is only accessible by authorised personnel. Passwords will be required to access the NAS, in compliance with the GDPR regulations. All manual files and written data will be stored in locked filing cabinets. All anonymized data will be stored for up to 10 years as recommended by the VUB.

### g) Specified retention period

All anonymized data will be stored for up to 10 years as recommended by the VUB.

### h) Other aspects of clinical quality assurance

In order to control the quality of the present study, the medical file of the participants can be consulted. If so, this will be done by qualified personnel who are bound to professional secrecy, e.g. representatives of the ethical committee or an external auditing bureau. This can only take place under strict conditions, under the responsibility of the investigator and under his supervision. The encrypted data can also be passed through the Belgium government or another regulatory authority or the ethical committee.

### 9. Amendments to the Clinical Investigation Plan

The study will be submitted to the commission of medical ethics at the University Hospital of the Vrije Universiteit Brussel. Moreover, it will also be registered in the Clinicaltrials.gov database. Once the clinical investigation is approved, they shall be notified to all proposed changes to the approved clinical investigation that have a substantial impact on the safety, health or rights of the subjects or on the robustness or reliability of the clinical data generated by the investigation, and that the response of no objection will be awaited, in accordance with ISO 14155:2020 and the procedure as laid down in article 75 of MDR 2017/745. All alterations of the present protocol, if accepted, will be communicated to the commission of medical ethics through the use of amendments. All of these amendments will be submitted through the Dycoflow system, and subjected to approval by the commission. The proposed changes will only be implemented if they are approved by the mentioned commission.

### 10. Deviations from Clinical Investigation Plan

- a) Statement specifying that the investigator is not allowed to deviate from the CIP

The investigator shall not deviate from the approved CIP during the study.

- b) Procedures for recording, reporting and analysing CIP deviations

Any adjustment to the CIP shall be notified via an amendment as stated in “9 Amendments to the Clinical Investigation Plan”.

- c) Notification requirements and time frames

The investigator shall notify and report any deviations from the approved CIP in a timely manner.

- d) Corrective and preventive actions and principal investigator disqualification criteria

If the investigator deviates from the CIP without notifying and reporting in a timely manner, the sponsor shall be contacted and disqualification of the investigator is required.

### 11. Device accountability

#### a) Description of the procedures for the accountability of investigational devices

The sponsor shall keep records to document the physical location of all investigational devices from shipment of investigational devices to the investigation sites until return or disposal. All of these records are controlled by the principal investigator. The name who received, used, returned or disposed of the device shall be notified, as well as the date of receipt and return of the device.

#### b) Procedures and particular materials and instructions for the safe return of investigational devices

The investigator, users, rehabilitation doctors and ortho-prosthetists are required to use the investigational device as it is explained in the IFU provided by the manufacturer.

At the end of the clinical investigation, the investigational device will be returned to the manufacturer using its secure case.

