| Inclusion criteria                 | 
 
• Age: 25 - 65 years
 
• Gender: men and women
 
• Level of amputation: unilateral transtibial
 
• Medicare Functional Classification Level: K3-K4
 
                          |
| Exclusion criteria                 | 
 
• Having metal implants
 
• Bilateral or additional upper-limb amputation
 
• Diabetic of amputation
 
• Neurological disorders
 
• Excessive stump pains and wounds
 
 |
| Date of first enrollment           | September 2023                                                                                                                                                                                                                                     |
| Duration of clinical investigation | At least 2 years                                                                                                                                                                                                                                   |
| Follow-up                          | No follow-up is included in this study                                                                                                                                                                                                             |

*Table 1: Overall synopsis of the clinical investigation*

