## h) Definition of completion of the clinical investigation

The clinical investigation will be considered as terminated when the proposed sample size is tested and is defined as the last visit of the last subject.

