## 6.2. Investigation device(s) and comparator(s)

### a) Description of the exposure to the investigational device

20 subjects are asked to do their rehabilitation process with the LUNARIS® and then to perform their daily activities with the LUNARIS® during a period of 6 months in total. They are also asked to perform the above mentioned activities with the LUNARIS® during 2 experimental sessions.

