### e) The follow-up period during the clinical investigation

The principal investigator and co-investigators are available during the entire duration of the experiment of each subject. Follow-up is provided for each subject during their participation via direct appointments or via other channels such as email or telephone calls.

- f) Address what specific medical care is appropriate to be provided for the subjects after the clinical investigation has been completed

There is no follow-up plan considered since subjects are doing the rehabilitation process as usual and perform their daily activities with the investigational device or with the most suited prosthesis for them. Subjects can contact our department after and during the experiment for any further questions.

- g) Address recommended follow-up for the subjects after the clinical investigation has been completed

There is no follow-up plan considered since subjects are doing the rehabilitation process as usual and perform their daily activities with the investigational device or with the most suited prosthesis for them. Subjects can contact our department after and during the experiment for any further questions.

- h) Address the final disposition or potential future use of samples obtained from subjects

All anonymized data will be stored for up to 10 years as recommended by the VUB.

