### 16. Suspension or premature termination of the clinical investigation

- a) Criteria and arrangements for suspension or premature termination of the whole clinical investigation or of the clinical investigation in one or more investigation sites

The clinical investigation will be considered as terminated when the proposed sample size is tested and is defined as the last visit of the last subject. As mentioned in the informed consent, subjects can stop or halt their participation at their convenience without any disadvantages.

The end of the clinical investigation or temporary study halt or early termination will be notified to FAMPH. In case of study end reporting this will be done within 15 days (and 24 hours if based on safety grounds). The study report will be submitted within one year of the end of the clinical investigation or within three months if early termination or temporary halt.

- b) Criteria for access to and breaking the blinding / masking code in the case of suspension or premature termination of the clinical investigation

The competent authorities shall be notified when the study will be terminated earlier than anticipated. Participation is voluntary, there can be no compulsion in any way. Even after subjects have signed, they can stop their voluntary participation.

- c) Requirements for subject follow-up and continued care

There is no follow-up plan considered since subjects perform the experiment with the novel investigated device or with the traditional prosthetic foot used in rehabilitation. Subjects can contact our department during and after the experiment for any further questions.

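### The protocol takes the LUNARIS back at the end of the investigation but waives aftercare because subjects are using it, so the stated reason fails for the LUNARIS arm, and the date of return is unclear

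*Protocol*

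**What the plan says.** **Return of the device.** Section 11 b) reads: "At the end of the clinical investigation, the investigational device will be returned to the manufacturer using its secure case". It gives no exception. Section 6.2 c) names the LUNARIS as the sole investigational device, so the rule reaches the LUNARIS arm only. Section 11 a) keeps device records "from shipment of investigational devices to the investigation sites until return or disposal"; retention by the subject is not among the outcomes listed.

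**Care after completion.** Section 6.4 f) and g) both answer: "There is no follow-up plan considered since subjects are doing the rehabilitation process as usual and perform their daily activities with the investigational device". The same sentence names the prosthesis best suited to the subject as the alternative. Both sections add: "Subjects can contact our department after and during the experiment for any further questions". The synopsis (section 1.5) says: "No follow-up is included in this study". Section 16 c), on continued care, says: "There is no follow-up plan considered since subjects perform the experiment with the novel investigated device or with the traditional prosthetic foot used in rehabilitation".

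**Exposure.** Section 6.2 a) says: "20 subjects are asked to do their rehabilitation process with the LUNARIS® and then to perform their daily activities with the LUNARIS", for six months overall. Under section 6.1 d), subjects enter when their rehabilitation starts and learn to walk on the allocated foot.

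**End of the investigation.** Under section 6.1 h), repeated in 16 a), termination "is defined as the last visit of the last subject". Section 6.3 g) gives the investigation a duration of 24 weeks for each subject.

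**The concern.** Sections 6.4 f) and g) are where the protocol says what happens to a subject once the investigation is over. The answer given is that nothing need be planned, and the reason depends on the subject having the foot. Section 11 b) takes that foot away at the point where aftercare would begin. The two statements cannot both hold for the LUNARIS arm.

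Subjects are at stake here, not the estimate. The protocol itself treats a change of foot as something that takes time:

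- Section 2 h) calls for fitting, alignment and practice of basic tasks with the LUNARIS.
- Section 3 says that one to two hours of familiarisation in the earlier study was too short.
- Section 6.1 d) bases the 12-week period partly on the time people need to get used to a new prosthesis.

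A LUNARIS subject who returns the foot faces such a change, and the visible text says nothing about how it is handled. The unclear date of return adds to this, because neither the site nor the subject can tell from the protocol when it will happen.

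**Working it through.** No power or effect-size formula applies. The check is a count and a comparison of sections.

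**Who is affected.** Sections 6.1 a), 6.2 a) and 6.2 b) give 20 LUNARIS subjects and 20 subjects who start on the SACH foot. 20 + 20 = 40, the number in section 6.3 h). The return rule therefore covers 20 of 40 amputees (20/40 = 50%), and 0 of the 20 comparator subjects. Section 6.3 c) recruits further subjects until 40 is reached, so 20 is the planned arm size.

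**Does the waiver's reason survive the return?**

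| Arm | Reason in 6.4 f) and g) | Effect of 11 b) | Reason after the end of the investigation |
|---|---|---|---|
| LUNARIS (20) | Daily life with the investigational device | Device goes back to the manufacturer | No longer true |
| Comparator (20) | Daily life with the best-suited prosthesis | None | Unaffected |

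**Is the change of foot covered elsewhere?** Section 6.1 d) lets the SACH group try other devices between weeks 12 and 24, and section 6.2 b) moves that group to the prosthesis that suits them best. Neither provision is made for the LUNARIS group. Sections 6.4 and 16 c) offer contact for questions. No other visible section says which foot a LUNARIS subject has after return, who supplies it or how the change is organised.

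**When is the foot returned?** Section 11 b) ties return to the end of the clinical investigation, and that term is used in two ways:

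1. For the whole study (6.1 h and 16 a), it ends at the last subject's last visit.
2. For each subject (6.3 g), it lasts 24 weeks, which fits the six months of LUNARIS use in 6.2 a).

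The two dates coincide only for the last subject to finish. For everyone else, 11 b) read with 6.1 h) gives a later return than 11 b) read with 6.3 g) and 6.2 a).

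**The case against.** The best reply is that the absence of study follow-up is not the absence of care. Subjects come from rehabilitation centres and orthopaedic departments (6.3 d), a certified prosthetist assembles and aligns the prosthesis (2 g), and the LUNARIS is a CE-marked device (4 c) used on prescription (2 a). Section 6.4 may simply leave later care to these services. The consent form, the investigator's brochure, the instructions for use and the clinical investigation agreement are not part of the visible text and could cover handover. This rules out any claim that care stops, but it does not repair the reason that section 6.4 actually gives.

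Four stronger readings are tempting, and the documents do not support them:

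- **That these people lose their only prosthetic foot.** Entry at the start of rehabilitation points that way. But sections 5 b) and 5 d) speak of a current prosthesis, and section 7 b) adjusts for a previously used one, so some subjects may have another.
- **That section 16 c) contradicts 11 b) just as directly.** Its reason describes the foot used during the experiment, which stays true after return, and it sits under suspension or early termination. It needs aligning, but the direct conflict is with 6.4 f) and g).
- **That the first subject may keep the foot for about 128 weeks** (104 weeks of enrolment plus 24). This is a ceiling for one subject, taken at the limit of an enrolment period expected to be under two years, and it conflicts with the six months in 6.2 a). It does not measure the problem.
- **That any use after week 24 would be unmonitored.** The event-recording commitments in 14 e) to g) carry no week-24 cut-off, and the charger sends device data to the manufacturer, although only for maintenance.

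**Conclusion.** The point holds as a contradiction between section 11 b) and section 6.4 f) and g), confined to the LUNARIS arm: 20 of 40 amputees as planned, and no comparator subject. Followed as written, the protocol removes the foot these subjects rehabilitated on, keeps a reason for having no plan that the removal has made untrue, and offers only an answer to questions. Some subjects may be left without a foot they are accustomed to; the text does not show how many. The date of return is a second, smaller defect, because the protocol uses the end of the investigation in two senses.

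The conclusion rests on the visible protocol and assumes that the unseen attachments do not settle the handover. If they do, the sections still have to be brought into line with them. The primary endpoint, sample size and analysis are not affected. The sponsor should correct this because it concerns subjects' safety and is cheap to put right.

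**What to change.** 1. Reconcile section 11 b) with section 6.4 f) and g) for the LUNARIS arm, and align section 16 c) and the follow-up line of the synopsis.
2. State in 11 b) whether return is tied to each subject's own last visit or to closure of the whole study, and make 6.1 h), 6.2 a) and 6.3 g) consistent with that choice.
3. For the LUNARIS arm, replace the reason that no longer applies with the handover arrangement agreed between the sponsor and the treating centres. If an attachment already holds this arrangement, refer to it. Which foot and what care a subject receives is for the treating clinicians, and this review proposes neither.
4. Check that the consent form tells LUNARIS subjects the same thing about return.

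The cost is an amendment of protocol wording under section 9, a check of the consent wording, and an agreement with the recruiting centres. Visits, sample size and analysis do not change.

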### 12. Statements of compliance

#### **Statement A**

We confirm that we are working in accordance with the ethical principles set out in the latest version of the "Helsinki Declaration", the "Good Clinical Practice" and the Belgian law of May 7, 2004 on experiments with human persons.

#### **Statement B**

We confirm compliance with the content of the CIP and other regional (e.g. EC) or national regulations.

#### **Statement C**

We confirm that the clinical investigation shall not start until approval is obtained from the EC and other regulatory authorities.

#### **Statement D**

We confirm that all requirements imposed by the EC or other regulatory authority shall be followed.

#### **Statement E**

We confirm that we possess an insurance certificate for Civil liability policy.

#### **Statement F**

A clinical investigation agreement is attached to this document.

### 13. Informed consent process

#### a) Description of the general process for obtaining informed consent

The approval of subjects to participate in the present investigation will be collected using an informed consent which will be designed using a template of the UZ Brussel.

Participants must go through the 'informed consent' document and approve it by means of a signature before the start of the study. Oral explanation will be given before the start of the study if requested.

#### b) Description of the informed consent process in circumstances where the subject is unable to give it

Not applicable.

### 14. Adverse events, adverse device effects, and device deficiencies

#### a) Definition of adverse events and adverse device effects

There are no disadvantages or risks associated with this research. Moreover, previous experiments with the Talaris Demonstrator (the LUNARIS® prototype, registered on B.U.N. 143201526629) have shown that there is a high willingness and motivation from the participants to participate in the experiments and no side or adverse effects were reported. Risks associated with the investigated medical device are reported in the Risk Management File.

#### b) Definition of device deficiencies

To date, no device deficiencies have been reported with the LUNARIS®. We are not yet able to give a concise summary of device deficiencies and thus not able to report any deficiency that might have led to a serious adverse event if appropriate action had not been taken, intervention had not occurred, or circumstances had been less fortunate.

#### c) Definition of serious adverse events

There are no serious adverse events anticipated that will lead to death, injury, permanent impairment or deterioration in health anticipated for this clinical investigation and use of medical device.

